## Methods and timing for assessing, recording, and analyzing the efficacy parameters:

Humoral immunity: The sera will be processed for the determination of neutralizing IgG titers to poliovirus types 1, 2 and 3, using a modified neutralization assay according to a standard protocol (Annex VI). To ensure reproducibility, the neutralization assays for each participant will be run on the same plate. Both positive and negative controls will be used. All samples will be tested in triplicate. This test will be performed in the Enterovirus Research Center in Mumbai, supervised by the principal investigator.

Serum IgA for poliovirus types 1, 2 and 3 will also be tested in the Enterovirus laboratory at the Centers for Disease Control and Prevention (CDC) using ELISA (protocol in Annex VII).

Mucosal immunity: The stool samples will be processed in the laboratories in India from the Global Poliovirus Laboratory Network, according to the standard protocol used in all network laboratories, which includes isolation, intratypic differentiation (ITD), and sequencing of polioviruses. All network laboratories are accredited each year by WHO, a process that involve an on-site inspection, proficiency testing, etc. [20].

The samples from crevicular fluid and an aliquot of each stool sample will be sent to the Enterovirus laboratory of the Centers for Disease Control and Prevention (CDC). Determination of sIgA in crevicular fluids and stool will be performed in the CDC laboratory because of the current absence of standardized protocols and technical accreditation in Indian laboratories. The protocols for both tests are included in Annex VII and VIII.

The ELISPOT testing will be done according to a standard protocol developed by the International Vaccine Institute (IVI) Korea[21] at the National Institute of Cholera and Enteric Diseases (NICED), Kolkata, India. NICED is an institute under Indian Council of Medical Research (ICMR), Government of India. The protocol for this testing is included in Annex X.

# Assessment of Safety

## Specification of the safety parameters:

All participants will be informed to contact the study personnel if the child requires medical care. Should a serious illness occur while enrolled in the study (requiring a physician's visit or hospitalization), parents will receive instructions on whom to contact within the study institutions.

## The methods and timing for assessing, recording, and analyzing safety parameters:

The study questionnaire will be used to record data during each visit, and for the preceding period, if applicable.

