## Description and justification for the route of administration, dosage, dosage regimen, and treatment period:

At study entry (day 0), subjects will be randomized to one of three study arms. Arm A will be vaccinated with one dose of bOPV administered by the oral route at day 0; arm B will receive one dose of IPV intramuscularly; and arm C will not receive any vaccination. At day 28, all subjects will receive a single dose of bOPV that serves as a challenge dose.

A study from India [18] and a review of mOPV clinical studies is available [19].

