# Trial Objectives and Purpose

## Mucosal immunity:

- To compare baseline mucosal immunity (through different methods) among three age groups with several degrees of protection acquired through immunization:
  - Infants 6-11 months of age will have received a few OPV doses
  - Children 5-6 years of age will have received multiple OPV doses in campaigns and are expected to have the highest levels of mucosal and humoral immunity
  - Children 10-11 years of age will not have received booster OPV doses for > 5 years. They are expected to have high antibody titers but may have waned mucosal immunity.
- To determine whether one dose of bOPV or IPV significantly reduces excretion of poliovirus types 1 and 3, respectively, following a challenge dose with bOPV, compared to an unvaccinated control arm.
- To determine whether one dose of bOPV or IPV significantly increases sIgA in crevicular fluids and stool samples, and to examine whether the increase in specific SIgA in these specimens is correlated to a reduction in excretion of Sabin poliovirus types 1 and 3 following the challenge with bOPV. This will allow evaluating the use of sIgA as a surrogate test for assessment of mucosal immunity.
- To determine the robustness of the mucosal immune response by study arm and age group, by measuring poliovirus antibody-secreting cells in an ELISPOT-spot assay 7 days after the administration of the study vaccine.

Humoral immunity:

- To determine whether one dose of bOPV or IPV will significantly increase seroprevalence and booster antibody titers compared to unvaccinated children.
- To assess whether one dose of IPV will significantly increase seroprevalence and antibody titers compared to a single dose of bOPV.
- To examine the correlations between antibody titers in blood and shedding of poliovirus after a challenge dose, for each vaccine study arm and age group.
- To examine the correlation between levels of IgA in serum and levels of secretory IgA in crevicular fluids and stool samples, before and after the booster vaccine dose, to gain further understanding on the mechanisms of mucosal immunity against poliovirus.
- To analyze correlations between levels of secretory IgA in crevicular fluids and stools and the ELISPOT test results, to better understand mucosal immunity against poliovirus.

Safety:

- To assess adverse events following vaccine administration.

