**Vaccine administration**:

Type of vaccine administered: Intramuscular (IPV) Oral (bOPV) No vaccine

Lot and Batch number: Exp date: ___ / ___/ ___ Time of administration: ___ : ___

If intramuscular IPV, site of administration: Right arm Left arm

Observation for 30 minutes after vaccine administration:

Temp ________ Any symptoms: Yes / No.

If yes, describe symptoms: _______________________________________________________

If intramuscular IPV: Swelling: None <1 cm 1-3 cm > 3 cm

Redness: None <1 cm 1-3 cm > 3 cm

Name and signature of vaccinator _________________________________________

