# Clinical exam

Child healthy? Yes / No *(If No, fill the adverse event form, and provide advice/referral)*

Since the last visit, - Has the child required hospitalization? Yes / No

- Has the child required a visit to a physician/clinic for health problems? Yes / No

If yes to previous hospitalization / physician visit, has the adverse event form been completed? Yes / No

Name and signature of investigator/physician:

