**Mucosal immunity study in Moradabad**

**Day 31- Household stool sample collection**

**Date of visit _____ / _______ / _______ Child ID number:**

**Sample collection**:

Stool sample collected? Yes / No

If sample not collected, explain reasons:

*(Note: contact supervisory SMO for action if family not available at home or sample not collected for other reason. A second visit may be required for stool collection).*

Date when sample was collected _______ / ______ / ______

Quantity sufficient ((≥10 g)? Yes / No

Cold chain maintained? Yes / No

Name and signature of person responsible for stool collection:

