**Mucosal immunity study in Moradabad**

**Day 35- Household stool sample collection**

**Date of visit _____ / _______ / _______ Child ID number:**

**Sample collection**:

Stool sample collected? Yes / No

If sample not collected, explain reasons:

(Note: contact supervisory SMO for action if family not available at home or sample not collected for other reason. A second visit may be required for stool collection).

Date when sample was collected _______ / ______ / ______

Quantity sufficient (≥10 g)? Yes / No

Cold chain maintained? Yes / No

Name and signature of person responsible for stool collection:

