**Mucosal immunity study in Moradabad**

**Day 42- Household stool sample collection**

**Date of visit _____ / _______ / _______ Child ID number:**

**Sample collection**:

Stool sample collected? Yes / No

If sample not collected, explain reasons:

(Note: contact supervisory SMO for action if family not available at home or sample not collected for other reason. A second visit may be required for stool collection).

Date when sample was collected _______ / ______ / ______

Quantity sufficient (≥10 g)? Yes / No

Cold chain maintained? Yes / No

Name and signature of person responsible for stool collection:

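### Safety recording is promised at each visit, but the three household forms after the day 28 challenge carry no health item, so scheduled enquiry beyond 15 minutes waits until day 56

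*Protocol*

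**What the plan says.** The Safety part of Trial Objectives and Purpose sets the aim: "To assess adverse events following vaccine administration". The methods-and-timing paragraph of Assessment of Safety gives the means: "The study questionnaire will be used to record data during each visit, and for the preceding period, if applicable". The section on source data makes the questionnaire the source document.

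On dosing, the protocol states: "At day 28, all subjects will receive a single dose of bOPV that serves as a challenge dose". Stool is then collected 3, 7 and 14 days later. Specification of the efficacy parameters calls days 31, 35 and 42 visits, and each household form has a field for the visit date.

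The forms in Annex V differ in what they ask:

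- The clinic forms for day 7 (a subset only), day 28 and day 56 ask whether the child is healthy now. They also ask about care since the last visit, for example "Has the child required hospitalization? Yes / No", and about physician or clinic visits. Each prompts for the adverse event form.
- The household forms, headed "Day 31- Household stool sample collection", "Day 35- Household stool sample collection" and "Day 42- Household stool sample collection", ask whether a stool was collected, why not if missed, the date, the quantity, the cold chain and a signature. They ask nothing else.
- For the first dose, the day 0 form provides "Observation for 30 minutes after vaccine administration". For the challenge, the day 28 form asks only about problems in the first 15 minutes.

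**The concern.** The safety text and the forms do not agree. Three contacts that the protocol itself calls visits have no safety content, and they fall in the two weeks after a live vaccine dose given to every child.

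This weakens a stated objective. For the IPV and control arms the challenge is the only bOPV dose in the trial, and for controls it is the only study vaccine. The risk summary names VAPP as the main serious event associated with oral vaccines and says the exact risk after bOPV is unknown. The adverse event form treats paralysis, anaphylaxis, hospitalization and death as serious, and serious events are to reach the sponsor within 24 hours. In practice that can happen only once someone on the study has learned of the event. Staff go to the households in this window, but nothing on their form tells them to ask.

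**Working it through.** No sample size, power or error rate is involved. The check sets the forms side by side and counts days.

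**Inputs.** Challenge on day 28 (dosage regimen section). Household visits on days 31, 35 and 42, and final visit on day 56 (Trial Design and Annex V). Enrolment of 110 in each of 9 cells, and 801 planned completers (Annex I).

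**Scheduled safety content after the challenge**

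| Contact | Days since challenge | Health content of the form |
| --- | --- | --- |
| Day 28, after the dose | 0 | problems within 15 minutes |
| Day 31 | 31 − 28 = 3 | none |
| Day 35 | 35 − 28 = 7 | none |
| Day 42 | 42 − 28 = 14 | none |
| Day 56 | 56 − 28 = 28 | current health, hospitalization, physician or clinic visit |

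Health items appear on 0 of the 3 household forms.

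**What the day 56 look-back covers.** The form asks about the time since the last visit without saying which visit that is.

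- If it is day 28, recall is 56 − 28 = 28 days. The form's own numbering of day 56 as the third study visit leans this way.
- If it is day 42, recall is 56 − 42 = 14 days, and no scheduled question covers days 28 to 42 beyond the 15-minute check. The efficacy section's use of the word visit leans this way.

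On either reading, an illness that resolved without medical care is never asked about, because the items cover only present health and use of care.

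**Recall with questions at the household visits.** The intervals become 31 − 28 = 3, 35 − 31 = 4, 42 − 35 = 7 and 56 − 42 = 14 days. The longest falls from 28 to 14 days, and no interval within the first 14 days after the dose exceeds 7.

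**Numbers of children and visits**

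- Enrolled: 9 × 110 = 990.
- IPV and control arms: 6 × 110 = 660. Controls alone: 3 × 110 = 330.
- Household visits: at most 3 × 990 = 2,970, or 3 × 801 = 2,403 counting planned completers only.

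**The case against.** The strongest reply is that other routes exist. Parents are told to contact study staff if the child needs medical care and are encouraged to use the study institution. A stand-alone adverse event form, not tied to any scheduled visit, records onset date and time and flags serious events. The household forms call for escalation to the supervisory SMO when a family is away or a sample is missed, so a death or hospital stay might well surface there. This stands, and it limits the point. A reader might infer that everything after the challenge rests on recall at day 56, and the documents do not support that. What rests on day 56 is scheduled, active enquiry. The other routes depend on the parent speaking first.

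A reader might also infer that staff see every child at these visits. The forms document a stool collection and do not show that the child is seen. Nor do the documents support an expectation that serious events will come to light four weeks late. That is a worst case, reached only if parents do not report and nothing emerges at the household visits.

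It can be argued that each visit means each clinic visit, since the rule ends with a qualifier and the day 56 form does not count household contacts. The efficacy section and the household forms use the word the other way, so the text needs reconciling on either view.

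Copying the clinic questions unchanged would still miss an illness that resolved without care, and stool collectors are not the physicians or investigators who sign the clinic health items. Both objections are sound, and the fix is shaped to meet them.

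Finally, safety is neither a primary nor a secondary endpoint, both vaccines are licensed, and no efficacy conclusion changes. That argues for a moderate weight. It does not remove the stated objective.

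**Conclusion.** The point holds in limited form. The safety section and the household forms contradict each other. As written, the plan has no scheduled health enquiry between 15 minutes and 28 days after the challenge, although staff make three household visits in that time. Capture in between depends on spontaneous reports from parents. The day 56 question adds to the gap because its starting point is undefined and because it omits resolved illness that needed no care.

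The size is 28 days of recall against an achievable 14, for up to 990 children. This assumes visits on the nominal days. How many events would be missed cannot be estimated from the document, which gives no event rates or reporting rates. The change is worth making because it serves a stated objective at little cost. The primary endpoint is not affected.

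**What to change.** 1. On the day 31, 35 and 42 household forms, add three yes/no items asked of the parent: any illness or symptom since the previous contact, any hospitalization, and any physician or clinic visit. A yes should carry the prompt already used on the clinic forms to complete the adverse event form, and notice to the supervisory SMO. Asking the parent avoids requiring a stool collector to judge whether the child is healthy.
2. On the day 56 form, add the same any-illness item and state which contact the look-back starts from.
3. Align the safety section with the forms, so that it is clear which contacts count as visits for safety recording.

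The cost is about a minute per household visit (an assumption), at no more than 2,970 visits, or about 2,403 with 801 completers. At one minute each, that is 2,970 / 60 = 49.5 hours at most across the trial. Stool collectors need brief training, and there is some added data entry. No visit, sample, staff post or treatment rule changes.

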## Procedures for eliciting reports of and for recording adverse event and intercurrent illnesses:

As discussed above, parents will be encouraged to use the study institution for medical services.

## The type and duration of follow-up of subjects after adverse events:

Should adverse events occur, referral and medical care will be provided.

# Statistics

## A description of the statistical methods to be employed, including timing of any planned interim analysis:

A statistical analysis plan is provided in Annex II

**Humoral immunity**: Chi-square to compare the proportion of children seropositive in each study arm and age group; non-parametric tests to compare the titer distribution among the study arms.

**Mucosal immunity:** Chi-square to compare the proportion of subjects excreting poliovirus type 1, type 2, and type 3 at each collection point among study arms and age-groups; non-parametric tests to compare the median titers of poliovirus shed by individuals at each study arm and age-group.

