## A diagram of the study design is shown below.

## A specific statement of primary and secondary endpoints:

The primary endpoint is reduction in excretion at days 3,7 and 14 post- challenge dose of vaccine poliovirus administered 28 days after a single dose of bOPV or IPV.

The secondary endpoints are:

- Increase of sIgA in gingival fluids and stools 28 days after a dose of bOPV or IPV.
- Increase in poliovirus antibody secreting cells (measured with ELISPOT) 7 days following a dose of bOPV or IPV.
- Seroconversion or antibody titer boosting 28 days following a single dose of bOPV or IPV.

A description of what kind of trial:

This is a randomized controlled unblinded trial.

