# Assessment of Efficacy

## Specification of the efficacy parameters:

Humoral immunity: Sera collected at study entry (day 0) and during the 7-, 28- and 56-day visits, will be examined for the presence (detectable) or absence of neutralizing antibodies to all three poliovirus serotypes. A reciprocal titer of 8 is considered to indicate the presence of neutralizing antibodies. In addition, a change from non-detectable (reciprocal <8) to detectable (reciprocal >8), or from below the highest dilution tested (reciprocal <1448) to the highest dilution tested (reciprocal >1448) will also indicate seroconversion. Although highest titre for neutralizing antibodies is 1024, we are taking end point dilution of half a log higher then 1024. This log of 10.5 is the highest observable titre and is being used because of high titres observed in this highly immunized population.

For participants with detectable antibodies, antibody boosting is defined as a >4-fold increase.

Mucosal immunity: Stool specimens will be collected at 0, 28, 31, 35 and 42 day visits. The samples will be examined for the presence or absence of polioviruses and other enteroviruses. In positive samples, the virus type will be determined following standard protocols from the World Health Organization (WHO) [20]. In addition, the amount (titration) of virus particles will be measured in those samples positive for poliovirus.

Semi-quantitative levels of sIgA in gingival fluid and stool samples will be determined using ELISA. High, medium and low levels will be determined and correlated in each study subject with serum antibody levels and with virus shedding after the challenge (Annex VIII-IX).

Additionally, in a subset of children 10-11 years of age, blood samples collected on days 0 and 7 will be tested to detect the amount of antibody-secreting lymphocytes specific for poliovirus using the ELISPOT technique.

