# 7. To account for drop-outs and ensure that sufficient subjects will complete all study requirements, we will enrol a total of 990 subjects, 110 per age-group (6-11 mo, 5-6 years and 10-11 years) and per study arm (IPV, OPV and controls).

# ANNEX II

Analytic plan

1. The primary endpoint of the study is reduction in excretion of poliovirus following a challenge dose of bOPV in subjects who have received a single dose of bOPV or IPV.

2. We will use chi-square test to compare the proportion of study subjects that excrete virus/or not following the challenge, in each study arm.

3. To use a conservative measure of p, we will apply a two-tailed test. We will also prepare 95% confidence intervals.

4. We will use non-parametric tests to compare the (median) amount of virus excreted after the challenge in each study arm.

5. We will also use non-parametric tests to measure and compare the distribution of antibody titers in serum (only for those with a positive titer; i.e., >1:8), among study groups and before and after treatment.

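### The between-arm comparison of serum titres names no adjustment for the day-0 titre, which costs precision on a secondary analysis but does not bias it

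*Protocol*

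**What the plan says.** The Statistics section of the protocol plans, for humoral immunity, a chi-square test on the proportion seropositive and "non-parametric tests to compare the titer distribution among the study arms". It adds: "A statistical analysis plan is provided in Annex II". Item 5 of that annex reads "We will also use non-parametric tests to measure and compare the distribution of antibody titers in serum", and qualifies this as "only for those with a positive titer; i.e., >1:8), among study groups and before and after treatment". Neither place names a baseline covariate, a change from day 0, or stratification by day-0 titre for the comparison between arms.

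The humoral objectives are comparative. One is vaccine against no vaccine; another is "To assess whether one dose of IPV will significantly increase seroprevalence and antibody titers compared to a single dose of bOPV".

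The baseline data exist. The efficacy parameters cover "Sera collected at study entry (day 0) and during the 7-, 28- and 56-day visits", and the Trial Design section has blood drawn from all children before vaccination and again at day 28 (the day-7 sample is for a subset only).

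The listed humoral secondary endpoint is "Seroconversion or antibody titer boosting 28 days following a single dose of bOPV or IPV", with this definition: "For participants with detectable antibodies, antibody boosting is defined as a >4-fold increase". Seroconversion is also defined as a change from an earlier state, either from undetectable to detectable or from below to at the highest dilution tested.

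**The concern.** In children who have already been immunised, the titre after a dose usually depends on the titre before it. A between-arm test on the day-28 titre alone leaves that child-to-child variation in the error term. The objectives ask about an increase, and the measurement that would sharpen the answer has already been collected and assayed, but the planned between-arm test does not call for it. At stake is a modest real difference in titre, for IPV or bOPV against control or for IPV against bOPV, being missed in a secondary analysis.

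**Working it through.** **The plan's own figure.** The only stated sample size is 89 completers per arm and age group (Annex I), set for shedding of 0.30 against 0.10 at two-sided α 0.05 and power 0.90. With unpooled variance, n′ = 78.8. The continuity correction gives n = (n′/4)·[1 + √(1 + 4/(n′·0.20))]² = 88.5, rounded up to 89, so the figure is reproduced. It says nothing about titres. It serves below only as the number per arm.

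**Inputs from the documents.** 89 per arm; two-sided α 0.05; highest observable titre 10.5 on the log2 scale (1448).

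**Inputs that must be assumed.** The titre SD, the correlation ρ between day-0 and day-28 titres, and the average shift.

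**Analytic size.** Relative to a day-28-only comparison, adjusting for baseline multiplies the error variance by 1 − ρ², while a plain change score multiplies it by 2(1 − ρ).

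| ρ | 1 − ρ² | Sample-size factor 1/(1 − ρ²) | 89 acts like | 2(1 − ρ) |
|---|---|---|---|---|
| 0.3 | 0.91 | 1.10 | 98 | 1.4 |
| 0.5 | 0.75 | 1.33 | 119 | 1.0 |
| 0.7 | 0.51 | 1.96 | 175 | 0.6 |

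The change score is worse than ignoring baseline when ρ is below 0.5. Adjustment never is, apart from the one degree of freedom it uses.

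**Simulated rank tests.** SD 2 log2, values limited to 2.5–10.5, mean log2 titres 7 to 9, 89 per arm, shift 0.85 log2 (2^0.85, about 1.8-fold):

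| ρ | Rank test on day-28 titre | Rank ANCOVA on day-0 titre | Gain in points |
|---|---|---|---|
| 0.3 | 0.77–0.78 | 0.80–0.81 | about 3–4 |
| 0.5 | 0.76–0.78 | 0.84–0.88 | about 9–10 |
| 0.7 | 0.76–0.79 | 0.95–0.96 | about 18–20 |

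With no true shift, rejection was about 3–6% for both tests. At a shift of 1.5 log2 (about 2.8-fold), power was 0.994–0.999 against 0.997–1.00. At 2 log2 (4-fold) both were 1.00.

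A second set (SD 2.5 log2, mean 8, 2-fold shift) agrees: 71% against 81% at ρ = 0.5, and 72% against 92% at ρ = 0.7.

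**Does the boosting endpoint make up the loss?** With a ceiling of 1448, a child starting above 1448/4 = 362 cannot show a more than 4-fold rise. In the second set, a chi-square test on that criterion had 32% power at ρ = 0.5 and 42% at ρ = 0.7, below even the unadjusted rank test. A child above 362 can still count as a seroconverter by reaching the highest dilution. When that route was also counted in a check run, power rose but stayed below the unadjusted rank test at ρ from 0.3 to 0.7.

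**The case against.** Four points can be made for the plan as it stands.

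- *The day-0 titre is used elsewhere.* A reader might infer that the plan ignores it altogether. The documents do not support that: seroconversion and boosting are both judged against the child's earlier titre, and Annex II item 5 also compares titres before and after treatment. The gap is confined to the between-arm titre comparison.
- *The wording is open.* Rank ANCOVA is itself non-parametric, so the text does not forbid it, and such detail is often left to an analysis plan. But the protocol names Annex II as that plan and Annex II is at hand. An analyst following its words would most naturally run an unadjusted rank test.
- *The loss depends on the chosen shift.* This stands. If the average rise is near the 4-fold scale used to define boosting for a single child, both tests have full power. At ρ = 0.3 the gain is small even for a modest shift.
- *The simulation is not the exact planned analysis.* This also stands. Item 5 restricts titres to positive ones, whereas the simulations keep children at the floor.

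A reader might also infer that vaccine differences will be read off before-after tests within each arm, without being tested. The documents do not say so: both places plan a comparison among study arms or groups. Nor do they show widely differing starting titres within an age group. The objectives suggest differences between age groups, but no within-age spread is given.

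**Conclusion.** The point holds as a matter of efficiency. The between-arm titre test leaves out a baseline that every child provides. It remains unbiased with correct size, so a reader who inferred a false-positive risk or a biased vaccine comparison would be wrong. The cost is a sample-size factor of 1/(1 − ρ²) on a secondary analysis, for example 1.10 at ρ = 0.3 and 1.96 at ρ = 0.7. In power, that is somewhere between 3 and 20 points for an average shift of 0.85 log2, and close to nothing from 1.5 log2 upwards. These figures rest on an assumed SD, correlation and shift, none of which the documents supply. The primary shedding analysis is not affected.

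**What to change.** In the humoral paragraph of the Statistics section and in Annex II item 5, name the between-arm titre test as a rank ANCOVA of the day-28 titre on study arm and the same child's day-0 titre for the same serotype. Run it within age group, and stratify by age group when groups are pooled. State that before-after changes within an arm are reported descriptively. A plain change score should not be the default, because it loses power when the correlation is below 0.5.

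The cost is wording only: no extra visits, samples or assays. Adjustment cannot restore information for children whose titres are at the ceiling.
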